#### Exclusion criteria

The subject must be excluded from participating in the trial if the subject meets any of the following criteria:

Concurrent participation in any other interventional clinical trial or participation in any other interventional trial within one month before enrolment into this trial.Diagnosis of immunodeficiency or is receiving systemic steroid therapy or any other form of immunosuppressive therapy within 7 days before enrolment into this trial.Known history of active TB (Bacillus tuberculosis)Hypersensitivity to pembrolizumab or comparable medicinal products or any of its excipients.Prior anti-cancer monoclonal antibody (mAb) therapy within one month before enrolment into this trial or who has not recovered (i.e., ≤ Grade 1 (NCI CTCAE Grade) at baseline) from adverse events due to agents administered more than one month earlier.Prior chemotherapy, targeted small molecule therapy, or radiation therapy within one month before enrolment into this trial or who has not recovered (i.e., ≤ grade 1 (NCI CTCAE Grade) at baseline) from adverse events due to a previously administered agent.a.) Subjects with ≤ Grade 2 (NCI CTCAE Grade) neuropathy are an exception to this criterion and may qualify for the study.b.) If subject received major surgery, they must have recovered adequately from the toxicity and/or complications from the intervention prior to starting therapy.Known additional malignancy that is progressing or requires active treatment. Exceptions include basal cell carcinoma of the skin or squamous cell carcinoma of the skin that has undergone potentially curative therapy or *in situ* cervical cancer.Active autoimmune disease that has required systemic treatment in the past 2 years prior to enrolment (i.e. with use of disease modifying agents, corticosteroids or immunosuppressive drugs). Replacement therapy (e g., thyroxine, insulin, or physiologic corticosteroid replacement therapy for adrenal or pituitary insufficiency, etc.) is not considered a form of systemic treatment.Evidence of interstitial lung disease or history of (non-infectious) pneumonitis that required steroids within the last 6 months before enrolment into this trial, or current pneumonitis.Active infection requiring systemic therapy.Suspected lack of complianceIs pregnant or breastfeeding, or expecting to conceive or father children within the projected duration of the trial, starting with the baseline visit through 120 days after the last dose of trial treatment.HIV, HBV or HCV infectionApplication of a live vaccine within one month of enrolment.Hypersensitivity to cisplatin or any of its excipientsAny potential relationship to the investigator/his deputy or to medical staff of the study team, to the coordinating investigator or is an employee of the study site

### Interventions

#### Experimental intervention

Patients will receive pembrolizumab intravenously for 12 months, in 3-week cycle (q3w) 200 mg, in combination with standard treatment (adjuvant radio-chemotherapy).

Radiotherapy: standard adjuvant radiotherapy (e.g. pN0 50 Gy; pN1 56 Gy; pECS + primary 66 Gy)

Chemotherapy with cisplatin: (according to the respective standard of the center)

Cisplatin cumulative dose 300 mg/m^2^ body surface according to Cooper et al./Bernier et al. (2, 3) orCisplatin cumulative dose: 280 mg/m^2^ body surface, e.g. Cisplatin 40 mg/m^2^ iv, weekly in 1-7^th^ week of treatment

#### Control intervention

Standard treatment (adjuvant radio-chemotherapy)

### Trial treatments

#### Radiochemotherapy

The standard treatment has to be started at day 1 (week 1) in both treatment arms and should follow national guidelines. All patients will be treated as respective clinic standard and receive best standard care.

#### Radiotherapy

Radiation is delivered using IMRT in respect to the clinic standard. Planning and delivery of IMRT can be performed using sequential boost (SeqB) or simultaneous integrated boost (SIB). Following is an example how the process could be using SeqB: All patients will be immobilized in supine position in thermoplastic head, neck, and shoulder masks in order to conduct treatment-planning CT scans (slice thickness 3 mm) to define the target volumes and the organs at risk (OAR). Radiotherapy will be given at linear accelerators or helical tomotherapy by use of isocentric techniques with intensity modulated radiotherapy (IMRT) with 6 MV photon beams (9). All patients receive conventional daily single doses of 2 Gy, and five fractions per week. The target volumes and doses are determined from surgical results, and from CT/MRI. Three clinical target volumes (CTV) are defined: CTV 66 (total dose 66 Gy) for high-risk regions (R1, ECS), CTV 56 (total dose 56 Gy) for intermediate-risk regions (tumor bed (R0), involved nodes without ECS), and CTV 50 (total dose 50 Gy) for low-risk regions (i.e., pN0 or nodes down to the clavicles in both groups). Planning target volume (PTV) was defined as the CTV plus a 5- to 10-mm margin to compensate variables of treatment setup and motion of internal organs (10, 11). In the case of anatomical boundaries and to the spinal cord, the distances are to keep personalization. PTV should not go outside the skin surface, and can be retraced from surface by 3 mm. In general, the volume definition of cervical lymph node levels should be performed using the RTOG head and neck lymph node atlas (www.rtog.org) and additional recommendations for delineation and selection of elective neck levels (12). The OAR contouring should be done according to the consensus guidelines of DAHANCA, EORTC, GORTEC, HKNPCSG, NCIC CTG, NCRI, NRG Oncology and TROG (13).

#### Chemotherapy

The q1w and q3w schedule will be allowed in the ADRISK and may be applied according to the respective standard of the center. The dosing and timing of chemotherapy to be used in this trial is outlined in **Table 2**. These options were chosen since the q3w schedule is not very common in Germany. However, the balancing of the cisplatin/RT doses will be reviewed permanently to rule out bias between the arms and the cisplatin schedule is used as a stratification criterion. A minimum of 200 mg/m^2^ cisplatin should be aimed at in all patients. An intravenous infusion (volume replacement) will be given as supportive therapy. All patients receive adequate antiemetic prophylaxis. The choice between q1w and q3w is left to the appraisal of the radiation oncologist, considering age, weight loss before radiation, creatinine clearance and performance status. In practice, various radiotherapists systematically use q1w cisplatin, and others use q3w cisplatin. In case of poor radiochemotherapy tolerability, the patients have to be hospitalized or receive a nasogastric intubation.

**Table 2 T2:** Cisplatin treatment.

Drug	Dose/Body Surface Area	Frequency Dose/Body Surface Area	Route of Administration	Regimen/Treatment Period
Cisplatin	300 mg/m^2^	q3w 100 mg/m^2^	inravenous infusion	days 1, 22, and 43
Cisplatin	280 mg/m^2^	q1w 40 mg/m^2^	intravenous infusion	days 1, 8, 15, 22, 29, 36, 43 1-7th week

Patients must meet the following criteria before each new cycle:

• No hematotoxicity of grade ≥2 (i.e. neutrophils >1500/μL, platelets >100.000/μL, hemoglobin ≥9 g/dl, if required after transfusion)• Recovery from any treatment-related grade 3/4 non-hematological toxicity (except alopecia) to baseline or ≤grade 1• No ongoing requirement for anti-diarrheic treatment• Bilirubin ≤3.0 x ULN• Transaminases ≤2.5 x ULN• No peripheral neurotoxicity of grade 3• Creatinine clearance ≥60 mL/min• No treatment delay of more than 3 weeks

Patients not meeting the above criteria on the date scheduled for the new cycle must suspend treatment with the anticancer drugs until they meet the above criteria. In the case of a cisplatin intolerance during RCT, it may be possible to switch to carboplatin. The administration of mitomycin is not permitted.

#### Pembrolizumab treatment

The experimental treatment to be used in this trial is outlined in **Table 3**. First cycle of pembrolizumab starts on day 1 of aRCT. Pembrolizumab should be administered at least 30 minutes prior to premedication for the chemotherapies. Furthermore, pembrolizumab should be administered prior to chemotherapy. Adverse events (both non-serious and serious) associated with pembrolizumab exposure may represent an immunologic etiology. These adverse events may occur shortly after the first dose or several months after the last dose of treatment. Pembrolizumab must be withheld for drug-related toxicities and severe or life-threatening AEs. Dosing interruptions are permitted in the case of medical/surgical events or logistical reasons not related to study therapy (e.g., elective surgery, unrelated medical events, patient vacation, and/or holidays). Subjects should be placed back on study therapy within 3 weeks of the scheduled interruption, unless otherwise discussed with the sponsor. The reason for interruption should be documented in the patient’s study record.

**Table 3 T3:** Pembrolizumab treatment.

Drug	Dose	Frequency Dose	Route of Administration	Regimen/Treatment Period
Pembrolizumab	200mg	q3w	intravenous infusion	Day 1 of each 3 week cycle over 51 weeks

Pembrolizumab should be administered on day 1 of every three-week cycle, repeat every 3 weeks (+/- 3 days; due to administrative reasons) until regular end of treatment (18 cycles, week 52), disease recurrence or premature termination for other reasons. All trial treatments can be administered on an outpatient basis, depending on the respective standard of the center. (Potential) outpatient basis means that trial treatments always take place in a clinic with medical personnel that is sufficiently trained for such emergency situations (e.g. severe infusion reactions). The appropriate emergency care is guaranteed and will be provided immediately. Pembrolizumab 200 mg will be administered as 30 minutes intravenous infusion every 3 weeks. Sites should make every effort to target infusion timing to be as close to 30 minutes as possible. However, given the variability of infusion pumps from site to site, a window of -5 minutes and +10 minutes is permitted (i.e., infusion time is 30 minutes: -5 min/+10 min).

### Informed consent procedure

Before enrolment in the ADRISK trial, the patient will be educated that participation is voluntary and that he/she may withdraw from the clinical trial at any time without having to give reasons and without penalty or loss of benefits. The patient will be informed by the treating physician about the treatment methods to be compared, the expected risks and benefits and alternative treatment methods. The patient should be provided enough time to think about the participation in the clinical trial. Before any trial specific actions, the patient’s written consent must be obtained by dating and signing the informed consent form by the trial patient and the physician.

### Randomization process

Randomization of patients between experimental and control arm is performed centrally *via* a secure web-based tool using a modified minimization procedure with stochastic component according to Pocock (14) in a 1:1 proportion. Stratification is performed using the tumor localizations: 1) oral cavity, 2) oropharynx, 3) larynx, or 4) hypopharynx. For patient with oropharyngeal carcinoma, the p16-marker is generally determined in routine procedures and will be used as sub-classifier 2+) and 2-) so that 5 strata will be used in total. Furthermore, a stratification according to the q3w vs. q1w schedule of chemotherapy will be applied. Randomization will be balanced according to trial site as well. The result of the successful randomization is immediately available *via* the randomization tool and is forwarded automatically to the investigator and the Clinical Trial Center Leipzig.

### Schedule of trial procedures

**Table 4** summarizes the trial procedures to be performed as planned or at unscheduled time points if deemed clinically necessary by the investigator.

**Table 4 T4:** Schedule of trial procedures.

Trial period	Baseline (BL)	V1 – V4 Safety Follow-up	C1 – C18 Pembrolizumab treatment		V5 – V12 (V13 - V16 optional) Efficacy/Safety Follow-up	SV1, SV2… Survival Follow-up
Time	ALL patients		only patients in EXPERIMENTAL arm		ALL patients	ALL patients AFTER disease RECURRENCE
day **–** 10 - day 0	weeks 1, 4, 7, 10 (+/- 3 days)	**day 1** (week 1) **of aRCT** Cycle 1	week 4 - 52 (every 3 weeks) (+/- 3 days) Cycles 2 - 18	month 3, 6, 9, 12 (+/- 7 days) month 15, 18, 21, 24 (+/- 14 days) every 6 months (+/- 28 days) thereafter - optional	every 6 months after recurrence
Administrative procedures						
Informed consent	X					
Eligibility criteria	X		X^1^			
Demographics/Medical history	X					
Registration Randomization	X^2^					
Prior/concomitant medication	X	X^3^	X	X	X	
Treatment						
Adjuvant radio-chemotherapy		X				
Pembrolizumab			X	X		
Anticancer therapy after recurrence						X
Clinical Procedures/Assessments						
Adverse Events		X^3^	X	X	X^4^	
Physical examination	X	X^3^	X	X	X	
Vital signs	X	X^3^	X	X	X	
ECOG status	X	X^3^	X	X	X	
Laboratory measurements	X	X^3^	X	X	X^5^	
Survival status; locoregional or distant recurrence, initiation of a new anti-cancer treatment		X^3^	X	X	X	X
Efficacy measurements						
Clinical endoscopic assessment	X				X	
CT or MRI Head and Neck	X				X^6^	
CT chest	X				X^7^	

V= visit; C= 3-week cycle (q3w) pembrolizumab infusion (and aRCT) starting on day 1 of each cycle; SV, survival visit.

^1^If results of laboratory procedures done at Baseline Visit are older than 10 days, new blood sampling are necessary prior to start of treatment with pembrolizumab. Furthermore, pregnancy test must be negative within 3 days prior to receiving the first dose of study medication.

^2^Randomization must be done by the day 1 (start of the trial treatment) at the latest.

^3^In control arm all clinical procedures/assessments should correspond with the experimental arm (three-weekly +/- 3 days) up to and including first efficacy follow-up (month 3 after randomization).

^4^In experimental arm: until 90 days following cessation of treatment, or up to initiation of a new anti-cancer treatment; in control arm: until 1^st^ efficacy-FU (month 3).

^5^Only at safety follow-up at week 56 (+/- 7 days) or at premature treatment ermination (one month (+/- 7 days) after termination) - in the experimental arm.

^6^Every 6 months only.

^7^Every 12 months only.

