### Study objectives

The primary objective of ADRISK is to show that addition of pembrolizumab to aRCT with cisplatin improves EFS compared with aRCT alone in locally advanced intermediate and high-risk HNSCC after surgery. The primary endpoint EFS is defined as time from randomization to the first event, i.e.:

locoregional or distant recurrence (relapse),occurrence of further malignant disease (independent from localization and type),death from any cause, andinitiation of a new anti-cancer treatment without a previous event (primarily in case of safety concerns/toxicities observed which must be addressed in the patient**’**s treatment).

Secondary goals of the trial are to show that addition of pembrolizumab to aRCT with cisplatin improves OS compared with aRCT alone in locally advanced intermediate and high-risk HNSCC and to assess toxicity and show that addition of pembrolizumab to aRCT with cisplatin is safe in terms of toxicity (early *and* late toxicity). The duration of patients**’** observation is planned for at least 24 months post randomization, but preferably until LPLV (last patient**’**s last visit after 24 months of observation) to collect endpoint-events as comprehensive as possible.

Within the trial PD-L1 and p16 (only at tumor site oropharynx) expression in tumor tissue will be characterized by immunohistochemistry to explore the relationship between tumor PD-L1 and p16 expression and response to treatment with pembrolizumab. Therefore, material collected during the tumor resection will be analyzed locally at trial site and validated by reference pathologists in the central lab.

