### Statistical methods

#### Estimation of sample size

We expected a 2yr EFS of 55% with aRCT alone based on Cooper et al. (3, 15) and Bernier et al. (2) and assumed proportional hazards. A hazard ratio of 0.6 corresponds to an increase in EFS rates (at ~2 years) from e.g. 55 to 70% - an effect size worth detecting. Requiring a 5% one-sided significance level and 80% power, we need to observe at least 93 events for inference with the log rank test or by Cox regression. Since the effect of the experimental treatment is expected to become apparent only after 3-4 months, and the power may be slightly reduced, we set a target of 100 events. The number of patients needed to observe this count depends on the times of accrual, follow-up as well as the strategy of FUP. After modeling the expected information flow and calculating the expected observed events since start of accrual (using the pooled EFS curve in Cooper et al. (3)), we specified the end of study after 2 years of last patient’s observation or when at least 100 events have been observed before that time.

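### Follow-up after month 24 is optional for event-free patients but scheduled for relapsed ones, so the required EFS events are not secured and late OS can be biased downwards

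*Protocol article*

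**What the plan says.** Table 4 (Schedule of trial procedures) has two follow-up columns that matter here. The efficacy and safety column covers all patients at months 3 to 24. After that its visits, V13 to V16, are "every 6 months (+/- 28 days) thereafter - optional". The survival column applies only to patients with disease recurrence, is "every 6 months after recurrence", and is not marked optional. Plan for further treatment adds that observation for OS continues after recurrence.

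Study objectives sets at least 24 months of observation per patient and, beyond that, "preferably until LPLV". It names OS as a secondary goal.

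Estimation of sample size states: "Requiring a 5% one-sided significance level and 80% power, we need to observe at least 93 events". To allow for a delayed effect, "we set a target of 100 events". The study ends 2 years after the last patient enters, or earlier if 100 events have been seen. The section says that the patient number depends on the follow-up strategy, and that the event flow was modelled from a published pooled EFS curve. That model is not shown.

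**The concern.** The number of EFS events rests on follow-up that the schedule does not require. The end-of-study rule can shorten the trial but cannot lengthen it, so a shortfall would simply be accepted.

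The second issue weighs more. After month 24, a patient who has relapsed has a scheduled survival contact, and a patient who has not has an optional one. Relapse strongly predicts death. If relapse-free patients drop out of observation at month 24 while relapsed patients stay, the late OS risk set is enriched for patients close to death. Kaplan-Meier and Cox regression both assume that censoring is unrelated to prognosis within arm, and here the schedule itself could break that assumption. No later analysis can recover survival status that was never collected.

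**Working it through.** **Inputs from the article.** 240 patients, 1:1; 2-year EFS 55% in control; HR 0.6, or 55% to 70%; one-sided 5%; 80% power; 93 events required, 100 targeted.

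**1. The plan's own figure.** Schoenfeld: events = 4(1.645 + 0.842)² / (ln HR)².
- HR 0.6: 94.8, so 95.
- HR implied by 55% to 70%, ln 0.70 / ln 0.55 = 0.597: 92.7, so 93. The stated figure reproduces.

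**2. Events secured by the mandatory 24 months.**
- 120 × 0.45 + 120 × 0.30 = 54 + 36 = 90, with SD about 7.4.
- Summing the two binomials: P(≥93) is about 37% and P(≥100) about 10%, before any loss to follow-up.
- Power at 90 events: 78.2% (HR 0.6) or 79.0% (HR 0.597). At 100 events with HR 0.6: 81.8%.
- With an assumed 5% or 10% loss by month 24: 88 or 86 events, power about 77%.

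**3. What the optional visits add.** Accrual time, loss and the hazard after month 24 are not stated, so these are assumptions. With 24 months' accrual, constant hazard and no loss, full uptake would give 119.9 events by the last patient's month 24 if the study did not stop at 100. The uptake needed for 93 events is then (93 − 90.2) / (119.9 − 90.2) = 9%, and for 100 events 33%. If the hazard after month 24 falls to a quarter and 5% are lost, the same step gives (93 − 88.1) / (95.9 − 88.1) = 63%. At 50% uptake, with 24-36 months' accrual, a later hazard of 25-100% of the earlier one and 0-5% loss, about 92 to 111 events are expected.

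**4. OS at 36 months.** Assumptions, none of them in the article: exponential EFS; a share of EFS events that are deaths without relapse (15-30%); exponential survival after relapse with mean m (14-20 months). Write f for the proportion event-free at month 24, r for those relapsed and alive, S24 = f + r, S36 for true OS at 36 months, a = r·exp(−12/m), and u for uptake of the optional visits. The Kaplan-Meier estimate tends to

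KM36 = S24 × [a + u(S36 − a)] / (r + u·f).

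Administrative censoring unrelated to relapse, including a stop at 100 events, does not change this limit. Worked case, 15% and m = 14:
- Control: f = 0.550, r = 0.168, S24 = 0.718, a = 0.168 × 0.424 = 0.071, S36 = 0.559.
 - u = 1: 55.9%.
 - u = 0.5: 0.718 × 0.315 / 0.443 = 51.1%, which is 4.8 points low.
 - u = 0: 0.718 × 0.424 = 30.5%, which is 25.4 points low.
- Experimental: f = 0.699, r = 0.117, S24 = 0.815, S36 = 0.698.
 - u = 0.5: 65.4%, 4.4 points low.
 - u = 0: 34.6%, 35.2 points low.
- Difference between arms: 13.9 points true, 14.3 at half uptake, 4.1 at none.

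A simulation over the assumed range (15-30%, 14-20 months, accrual 24 or 36 months) gave a shortfall per arm of 3.4 to 4.8 points at half uptake, 7.5 to 10.6 at a quarter and 18 to 35 at none.

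**5. OS hazard ratio.** With 15%, m = 14, 36 months' accrual and the study stopped at 100 events, the HR was 0.61, 0.62, 0.64 and 0.70 at full, half, quarter and no uptake. OS power was about 65%, 66%, 62% and 45%. Over the wider range without the event stop, the HR was 0.61-0.64 at full or half uptake, 0.63-0.66 at a quarter and 0.66-0.73 at none.

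**The case against.** The best defence has four parts.

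- **Intent.** Study objectives wants observation to last-patient-last-visit so that events are collected as fully as possible. Visits after month 24 cannot apply to the last patients enrolled, so the word optional may partly reflect staggered entry. This stands as evidence of intent, but a preference is weaker than a requirement, and the survival column carries no such qualifier.
- **Small event shortfall.** Three events below 93 cost 1 to 2 points of power, and some uptake would often recover them. This stands. A reader might infer that the trial will miss its events; the article supports only that they are not secured.
- **The end-of-study rule.** A reader might compare the 90 events with the 120 to 150 that full follow-up to last-patient-last-visit would yield, or compare late OS with an estimate at 48 months. That is not the design. With constant hazard and full follow-up, 100 events arrive at about month 40, 47, 54 or 61 for 2, 3, 4 or 5 years' accrual, and the study stops there. Nor are the survival visits open-ended: they stop when the study does.
- **The OS analysis.** The planned analysis is a Cox model, and its hazard ratio barely moves with half the optional visits made. Censoring rules belong in the analysis plan. Both statements are fair. They limit the damage to the comparison, but they do not protect the survival curves, and an analysis plan cannot supply missing survival status.

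**Conclusion.** The point holds as a cheap improvement, not as a flaw that undermines the trial. The required schedule secures an expected 90 EFS events, not 93 or 100, at a minor power cost. The larger exposure is OS: censoring after month 24 depends on relapse to the extent that event-free patients skip optional visits, and the Kaplan-Meier curves are then biased downwards. The direction follows from the schedule. The size rests on uptake, which the article does not give, and on the assumed share of deaths without relapse and survival after relapse. The bias vanishes only with full uptake.

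A reader might conclude that the OS comparison between arms is invalid. The documents do not support that: the hazard ratio is close to its full-follow-up value at half uptake, shifts slightly at a quarter, and moves materially towards 1 only when uptake is very low.

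**What to change.** In Table 4, replace the optional visits after month 24 with a mandatory 6-monthly status contact for every patient until the end of study defined in Estimation of sample size. This includes contacts beyond month 48 (V16) if the study is still open. The contact should record survival, recurrence, new malignancy and new anti-cancer treatment; a telephone call or records check is enough. Align Study objectives, Table 4 and Estimation of sample size so that all three state the same follow-up.

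If this cannot be done, censor OS by one rule that does not depend on relapse, for example at month 24 for all patients, relapsed ones included, and restate the secured number of EFS events as about 90.

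The first option costs a brief contact every 6 months for event-free patients after month 24, plus amendment wording. The fallback costs nothing to run but gives up late OS information.

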#### Planned methods for analysis

Confirmatory analysis follows the intention to treat principle and will be based on the full analysis set. Time to event endpoints will be analyzed by Cox regression with arm as fixed effects, stratification criteria as fixed and center as random effect. The occurrence of safety endpoints (AE by Preferred Term/occurrences of toxicities of grades ≥3) will be compared by chi-square tests. Odds ratios with 95% confidence intervals will be provided. Serious adverse events will be reported descriptively (including a clinical causality assessment) by System Organ Class and Preferred Term according to MedDRA. In case of relevant frequencies of SAE and classified serious adverse reactions (by Preferred Term) exact Fisher test will be applied on SAE/SAR occurrences. No confirmatory subgroup analyses are planned. PD-L1 status will be analyzed in exploratory analyses. Safety issues will be carefully monitored. Regular safety analyses will be performed and presented to the Data-Monitoring Committee (DMC). Statistical monitoring will focus on data quality assurance. All analyses will be pre-specified in a detailed statistical analysis plan, which will be finalized before data base closure. The trial will be reported according to CONSORT criteria.

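### Adverse events are recorded to month 3 in the control arm but for up to about 447 days in the experimental arm, so crude occurrence tests overstate excess toxicity and late toxicity has no concurrent comparator

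*Protocol article*

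**What the plan says.** Four places bear on this point.

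- **Collection window** (Schedule of trial procedures, Table 4, footnote 4): in the experimental arm, recording runs until 90 days after "cessation of treatment, or up to initiation of a new anti-cancer treatment; in control arm: until 1^st^ efficacy-FU (month 3". Pembrolizumab itself runs "until regular end of treatment (18 cycles, week 52", which the section on further treatment gives as 51 weeks.
- **Other control-arm assessments** (same table): footnote 3 matches them to the experimental arm at three-week intervals, "up to and including first efficacy follow-up (month 3 after randomization". Footnote 5 limits laboratory tests during later follow-up to the experimental arm: "Only at safety follow-up at week 56" or one month after premature termination.
- **Analysis** (Planned methods for analysis): "The occurrence of safety endpoints (AE by Preferred Term/occurrences of toxicities of grades ≥3) will be compared by chi-square tests". Each comparison also gets an odds ratio and its 95% confidence interval, and Fisher's test is applied to SAE/SAR occurrences where frequencies are relevant. Neither a common counting window nor a method for time at risk is named.
- **Objective** (Study objectives): the trial is to show that adding pembrolizumab "is safe in terms of toxicity (early *and* late toxicity".

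**The concern.** A chi-square test on the proportion of patients with at least one event is a fair comparison only if both groups were watched for the same length of time. Here the watching stops much earlier in one arm, and it does so by rule rather than by chance. An event type with the same true hazard in both arms would then look more frequent with pembrolizumab. Late effects of the radiochemotherapy that both arms receive would be counted in one arm only.

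Following pembrolizumab patients for longer is sensible, since the protocol expects immune-related events some months after the last dose. The difficulty is that the objective, the data collection and the test do not fit together. Part of this can be repaired at analysis by counting to month 3 only. The other part cannot, because control-arm events after month 3 are never recorded, and an analysis plan cannot supply them.

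**Working it through.** **Plan's own figure.** There is none to reproduce. The article states no adverse event rate and no safety power; its only power figure (93 events) concerns event-free survival and has no bearing here.

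**Observation windows.**
- Control: month 3, taken as 91 days.
- Experimental, 18 cycles completed: 51 × 7 + 90 = 357 + 90 = 447 days (14.7 months). Ratio 447 / 91 = 4.9.
- Experimental, stop at about week 25: 168 + 90 = 258 days (8.5 months). Ratio 2.8.
- Experimental, stop in week 7: 42 + 90 = 132 days (4.3 months). Ratio 1.45.

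**Check 1: equal constant hazard.** Assume no true difference, 120 patients per group (240 randomized 1:1) and a three-month risk q. The experimental-arm risk over T days is p = 1 − (1 − q)^(T/91). The odds ratio is [p/(1 − p)] / [q/(1 − q)]. For q = 2% and T = 447: p = 1 − 0.98^4.91 = 9.4%, and the odds ratio is (0.0945/0.9055) / (0.02/0.98) = 5.1. Rejection rates below come from exact enumeration of the two binomial counts, two-sided at 5%.

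| Three-month risk | Window (all patients) | Experimental risk | Odds ratio | Rejection, uncorrected | Rejection, continuity-corrected |
|---|---|---|---|---|---|
| 1% | 14.7 months | 4.8% | 5.0 | 41% | 25% |
| 2% | 14.7 months | 9.4% | 5.1 | 74% | 62% |
| 5% | 14.7 months | 22% | 5.4 | 98% | 97% |
| 2% | 8.5 months | 5.6% | 2.9 | 28% | 18% |
| 2% | 4.3 months | 2.9% | 1.5 | 6% | 2% |

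With equal windows and a 2% risk, the same enumeration of the uncorrected test gives 4%, so the 6% in the last row is close to what the test does without any bias.

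**Check 2: acute phase, then a low late hazard.** Assume the same three-month risk q in both arms, then a late hazard of 1% per month in both arms, with all experimental patients observed for 14.7 months. The extra time is 14.7 − 3 = 11.7 months, so p = 1 − (1 − q) × exp(−0.01 × 11.7) = 1 − (1 − q) × 0.89.

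| Three-month risk | Experimental risk | Odds ratio | Rejection, uncorrected |
|---|---|---|---|
| 5% | 15.5% | 3.5 | 79% |
| 10% | 19.9% | 2.2 | 59% |
| 30% | 37.7% | 1.4 | 24% |
| 60% | 64.4% | 1.2 | 11% |
| 80% | 82.2% | 1.15 | 7% |

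The distortion is large for uncommon or late-onset terms and small for common toxicities that mostly occur before month 3.

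**The case against.** The analysis section names a test but does not say that events are pooled over each arm's full collection window. The article defers detail to a statistical analysis plan that is not shown, and such a plan could restrict the counts to month 3. The data for that comparison are secured, because both arms are assessed every three weeks until then. This stands for early toxicity, and it means that bias in the early comparison is not inevitable. It does not stand for late toxicity, where the control data will not exist.

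A reader might infer more than the documents support:

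- *That the experimental arm is observed for about 15 months.* This is the maximum. Stopping treatment early, recurrence or a new anti-cancer treatment shortens it, and the false-positive rate then falls quickly. Radiochemotherapy lasts at most seven weeks, so much of the toxicity shared by both arms should fall inside the common window.
- *That the safety objective as a whole cannot be answered.* Early toxicity can be compared.
- *That the Data-Monitoring Committee would see distorted tables.* The article mentions regular safety analyses but does not describe their layout.
- *That control patients have no safety follow-up after month 3.* They attend visits through month 24 with physical examination, vital signs, performance status, medication review and endoscopy. These are not adverse event records, but the visits take place.

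The bias also runs against pembrolizumab, so it could not by itself produce a false claim of safety, and the analysis of event-free survival is untouched.

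**Conclusion.** The point holds in a limited form. As written, a crude occurrence comparison over unequal windows overstates excess toxicity with pembrolizumab for any term that can first occur after month 3. The late part of the toxicity objective has no concurrent comparator, whatever the analysis plan says. The windows come from the document. The false-positive rates do not: they rest on assumed event rates, equal hazards, 120 patients per group and one common window length for all experimental patients. For a 2% three-month risk at constant hazard they run from about 6% to about 74% according to how long patients stay on treatment. They should be cited as that range and not as the upper figure alone.

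**What to change.** 1. State in the analysis section or the analysis plan that between-arm chi-square tests, Fisher tests and odds ratios count events from randomization to the month 3 visit only. This costs one sentence.
2. For events after month 3, choose one of two routes:
   - Report later experimental-arm events descriptively without a between-arm test, and limit the comparative safety objective to early toxicity. This needs only a change of wording, but gives up the late comparison.
   - Where still possible, record at least grade 3 or higher events and late radiation effects in control patients at the already scheduled month 6 to 24 visits, and compare the arms over a common window with time-at-risk methods (cumulative incidence or exposure-adjusted rates). This adds no visits, but it amends data collection in a trial that has been recruiting since August 2018. Control patients already past month 3 will have incomplete late data, and the report must say so.
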